## Introduction

Chemotherapy-induced peripheral neuropathy (CIPN) is a persistent cancer treatment-related side effect that negatively impacts physical functioning, falls, and quality of life [1–4]. CIPN typically affects the hands and/or feet, with numbness, tingling, pain, cold hypersensitivity, and muscle weakness among the most common sensory and motor symptoms [5, 6]. CIPN is estimated to occur in 25%-90% of patients during chemotherapy and persists in many survivors long-term [7–9]. Multiple classes of neurotoxic chemotherapy drugs are associated with CIPN, including taxanes, platinum derivatives, and vinca alkaloids [10]. The etiology and natural history of CIPN are heterogeneous across classes of neurotoxic chemotherapeutic agents [11, 12]. Not all patients receiving the same neurotoxic treatment regimen will develop CIPN, but for those who do, symptom severity and recovery after treatment vary widely [13].

Cancer survivors with CIPN have worse physical functioning (e.g., mobility), more self-reported disability, and significantly higher fall rates than asymptomatic survivors [4, 7, 14]. In a cross-sectional study of breast cancer survivors approximately 6 years post diagnosis, distinct patterns of worsening objective and patient-reported physical function, disability, and fall risk were associated with increasing CIPN severity [4]. Most studies reporting mobility impairments due to CIPN have multiple limitations: cross-sectional design, reliance on complex measures that are impractical to capture in a clinic setting, and lack of power to capture falls. Moreover, these studies do not examine heterogeneity across patients, which may be central to identifying patients at greatest risk for poor outcomes [4, 15, 16]. Longitudinal studies reporting trajectories of CIPN symptoms and mobility deficits have been conducted, but none have linked mobility impairments to falls or the onset of disability [17, 18]. Additionally, it remains unknown when CIPN symptoms become severe enough to impair functioning and increase fall risk.

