## Methods

### Study aims and hypotheses

Our study aims and hypotheses are three-fold: (1) Characterize the variability in trajectories of CIPN symptoms and physical functioning in patients across treatment and 1 year of recovery. We hypothesize that there will be significant congruence between worsening CIPN symptoms and declining physical activity, mobility, and self-reported physical functioning and disability; (2) Identify 2 or more distinct trajectories of change in symptoms and functioning associated with significant differences in fall rates. We hypothesize that we can identify 2 or more distinct trajectories of CIPN and physical functioning associated with falls; and (3) Identify the simplest set of predictors that identify patients at risk for CIPN-related functional decline and falls. We hypothesize that some combination of patient characteristics (e.g., age, sex, comorbidities, body mass index), chemotherapy features (e.g., chemotherapy drug class, number of chemotherapy cycles, cumulative chemotherapy dose), and mobility measures (gait, balance) will predict distinct trajectories of change in CIPN symptoms and physical functioning [9, 19, 20].

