#### Specific analysis plan

The analysis will proceed in a series of stages.

*Hypothesis 1.1:Worsening neuropathy symptoms will be associated with concomitant worsening in functioning. *

The change over time in each symptom and functioning outcome will be modeled using a mixed-effects modeling framework implemented in the lme4 statistical package for R. The fixed and random effects structure and the shape of change across time (e.g., linear versus nonlinear) will be determined through likelihood ratio model testing and information criteria. Intercepts (initial status) and growth estimates (e.g., linear and/or quadratic trends) will be estimated for each individual patient for each outcome. All pairs of neuropathy symptom and functioning intercepts and slopes will be correlated to test Hypothesis 1.1*.*

*Hypothesis 1.2. At least two classes of patients with distinct trajectories of change in symptoms and functioning can be identified, and will be associated with significant differences in fall rates.*

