Once we characterize the variability in symptom and functioning trajectories, we will determine the simplest set of predictors that identify patients at risk for CIPN-associated functional decline and falls. We will consider multiple patient, behavioral, and clinical attributes that may increase predictive capacity for CIPN. Several possible risk factors that increase the likelihood of developing CIPN have been suggested, including comorbidities, age, smoking, obesity, and inactivity [9, 19, 20]. Cross-sectional studies have identified single attributes associated with higher CIPN, but only a longitudinal study can differentiate between causal factors and co-occurring problems to identify which and why patients are at risk for CIPN, associated mobility problems, and/or falls. We will also evaluate whether treatment characteristics (e.g., number of cycles, cumulative dose, etc.) and simple mobility tests (e.g., TUG) that can quickly be performed in a clinic setting improve predictive power.

Determining how, when, and in whom neurotoxic cancer treatment increases the risk of falls and disability will provide a more nuanced and comprehensive understanding of the presentation and progression of treatment-related impairments. Early identification of simple, early predictors of functional decline and developing fall risk would enable providers to closely monitor those patients at greatest risk of developing CIPN that becomes severe enough to limit mobility and increase fall risk. This knowledge would also facilitate shared decision-making between providers and patients regarding balancing clinical outcomes and quality of life during treatment planning. Incorporating simple measures of impending functional decline into clinical pathways would alert providers when symptoms progress enough to warrant interventions such as dose reductions, switching treatments, and/or referral to rehabilitation. Identifying which mobility deficits to target would contribute to an evidence base for preventive and rehabilitative programs that improve function and in turn lower fall and disability risk. Collectively, these practices would mitigate disability and falls associated with cancer treatment and improve quality of life in cancer survivors.

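### Hypothesis 1.1 claims concomitant worsening, but its stated test, correlating patients' growth terms, does not test concurrency and estimates neither a lag nor a severity threshold

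*Protocol article*

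**What the plan says.** In the Protocol article, Specific analysis plan, Hypothesis 1.1 reads: "Worsening neuropathy symptoms will be associated with concomitant worsening in functioning". Each symptom and functioning outcome gets its own mixed-effects model. On the form of growth, "the shape of change across time (e.g., linear versus nonlinear) will be determined through likelihood ratio model testing and information criteria". From each model, "Intercepts (initial status) and growth estimates (e.g., linear and/or quadratic trends) will be estimated for each individual patient for each outcome". The test is then named: "All pairs of neuropathy symptom and functioning intercepts and slopes will be correlated".

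Study aims and hypotheses puts the same idea more loosely: "We hypothesize that there will be significant congruence between worsening CIPN symptoms and declining physical activity, mobility, and self-reported physical functioning and disability". The Introduction gives a timing and severity question as an open gap: "it remains unknown when CIPN symptoms become severe enough to impair functioning and increase fall risk". The Abstract also lists the timing of risk and of early intervention among the gaps that the study will address, and the Discussion expects the results to show when in care to intervene.

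Under Procedures, symptom surveys are weekly. Clinic tests and functioning surveys fall at each clinic assessment: every 4–6 weeks in chemotherapy, then at about 3, 6, 9 and 12 months.

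**The concern.** The named test works across patients. It takes a few numbers per patient per outcome, each summarising the whole of follow-up, and asks whether patients with more symptom growth also have more functional decline. *Concomitant* worsening is a statement about time within a patient: function falls as that patient's symptoms rise. A patient whose function drops a season after symptoms appear can have growth terms much like those of a patient in whom both change together.

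No other stated analysis fills the gap. The latent class stage reuses the same intercepts and growth terms, and the survival models concern time to first fall, not onset of functional decline. Significant correlations could therefore be reported as concomitant worsening when function in fact lagged, and the severity question in the Introduction would have no analysis behind it, although the paired data are collected.

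**Working it through.** **Power figure.** The plan gives none for Hypothesis 1.1. Its d = 0.40 under Sample size/power calculation concerns class comparisons and does not bear on this point.

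**Detectable correlation.** With 80% power and two-sided α = 0.05, r = tanh[(1.960 + 0.842)/√(N − 3)].
- N = 200: 2.802/14.04 = 0.1996, so r = 0.197.
- N = 160 (the plan's complete-case figure): 2.802/12.53 = 0.2236, so r = 0.220.

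**Simulation A: how far a delay changes the correlations.** Visit spacing follows Procedures; the other inputs are assumptions:
- 200 patients and 60 replicates; chemotherapy lasting 3–6 months; weekly symptoms; function about every 5 weeks in chemotherapy, then at 3, 6, 9 and 12 months;
- symptom onset at mean 2 months (SD 1), a rise over 2 months that persists, and a magnitude varying between patients (gamma, shape 2, scale 1);
- functional loss of 0.8 × symptom magnitude plus noise (SD 0.6), starting 0, 3, 6 or 9 months after symptom onset;
- visit noise SD 1.0 (symptoms) and 0.7 (function); growth terms fitted per patient by least squares.

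Both measures are coded so that worsening is positive. Brackets give the central 95% of replicates.

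| Delay (months) | Linear model: slope | Quadratic model: linear term | Quadratic model: quadratic term |
|---|---|---|---|
| 0 | 0.75 (0.68 to 0.81) | 0.67 (0.58 to 0.75) | 0.56 (0.44 to 0.65) |
| 3 | 0.72 (0.64 to 0.78) | 0.55 (0.45 to 0.66) | 0.34 (0.21 to 0.50) |
| 6 | 0.69 (0.61 to 0.76) | 0.18 (0.06 to 0.33) | -0.20 (-0.33 to -0.09) |
| 9 | 0.60 (0.49 to 0.70) | -0.33 (-0.48 to -0.20) | -0.54 (-0.66 to -0.44) |

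With linear growth, delays of 0 and 6 months overlap, and even 9 months lies far above 0.22. With quadratic growth, a 3-month delay still passes easily, while longer delays weaken and then reverse the terms. No coefficient is a delay in weeks or a symptom level.

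**Simulation B: linear growth.** There were 160 patients, 8 visits (an assumed number) and 200 runs, with growth terms as best predictors from the mixed model. Function is coded so that loss is negative. The comparator is a visit-level within-person model on the concurrent symptom score.

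| Delay (weeks) | Slope correlation | Significant | Concurrent within-person term significant |
|---|---|---|---|
| 0 | -0.37 | 89% | 100% |
| 12 | -0.41 | 95% | 81% |
| 26 | -0.34 | 95% | 20% |

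With no coupling, the two methods were significant in 5–6% and 4–7% of runs.

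**Simulation C: quadratic growth.** There were 160 patients, with ranges across assumed settings. At no delay the correlations were -0.42 to -0.49 (linear term) and -0.40 to -0.44 (quadratic term). At 12 weeks they were -0.38 to -0.40 and -0.26 to -0.37, significant in 93–100% of runs. At 26 weeks they weakened. The concurrent within-person term was significant in 30–87% of runs at 12 weeks.

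**Rise and recovery with no delay.** When 50–100% of the symptom resolves, the linear-slope correlation is weak: +0.03 (significant in 24%) under simulation B's settings, and -0.18 and -0.09 at two noise levels in a further check with 160 patients, 9 visits and 40 runs per level. In that check the likelihood ratio test chose the quadratic model in every run for both measures. The growth-term correlations were then -0.61/-0.62 and -0.41/-0.41, significant in 98–100% of runs.

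**The case against.** The strongest defence is that Aim 1 speaks of congruence, and correlated growth terms are a recognised between-patient test of that. The timing sentences are background and discussion; none of the three aims promises a lag or a threshold. This stands in part, and is why the correlations should be kept. It does not cover the word *concomitant* in the hypothesis that the test is named for. Nor is this detail left to an unseen analysis plan: the article states both the hypothesis and its test.

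A reader might infer that the plan reduces each patient to one slope, discards timing and cannot tell simultaneous from late decline. The document does not support that. It allows nonlinear shapes and quadratic terms, and in simulation those terms respond to long delays. A reader might also infer that simultaneous rise and recovery would show no correlation. That follows from forcing a straight line on the course, and the plan's own shape selection largely removes it.

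The Discussion's sentence that "only a longitudinal study can differentiate between causal factors and co-occurring problems" may look like further evidence. It concerns patient attributes as risk factors for neuropathy, not the order of symptoms and function, so it carries no weight here.

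Two further objections stand and limit the remedy. The concurrent within-person term is itself often significant at a 12-week delay (81% in simulation B, 30–87% in C), so it cannot establish concurrency alone. And surveys start at enrolment, so a score from 12 weeks earlier is missing for the assessments at weeks 0, 4 and 8 with 4-week spacing, or weeks 0 and 6 with 6-week spacing. The joint class model will describe change over time by class, which helps descriptively but estimates no lag.

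**Conclusion.** The concern holds in limited form. The stated test of Hypothesis 1.1 addresses correlated overall change between patients. It does not test whether worsening is concurrent within a patient, and it estimates neither a lag nor a severity threshold. A delay of about 3 months would usually still give clearly significant correlations under quadratic growth, and also under linear growth unless most of the symptom resolves. Longer delays weaken the quadratic terms, so timing is blurred rather than lost.

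How far delays can be told apart depends on onset, size and noise, which the article does not give and which were assumed here. That the test contains no estimate of lag or threshold follows from the stated method and needs no simulation. The planned correlations remain valid for congruence; what they cannot carry is the concomitant claim or the timing and severity questions.

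**What to change.** Keep the growth-term correlations as the between-patient test of congruence. Add, for each function measure, a mixed model at the level of the assessment:

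- the weekly symptom score as a time-varying predictor, split into the patient's mean and the deviation from it, with time effects;
- concurrent and earlier-week scores (for example 4 and 12 weeks before) compared in the same model, because the concurrent term alone can be significant under a lag;
- symptom categories in place of the linear score, to address the severity question in the Introduction.

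This uses data already scheduled and costs wording, programming and a few more models to report. The report should say that longer lags are unavailable for the early assessments. If the added models are not wanted, restrict the conclusion from Hypothesis 1.1 to correlated overall change and do not describe the worsening as concomitant.

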 Each patient's intercept and growth estimates for each measure will be entered into a GMM to identify patient clusters with distinct symptom and function trajectory profiles. For each patient, a probability of belonging to each latent class will be assigned, and the highest membership probability will be used to make a final class assignment. Identification of the best-fitting model will be based on information criteria (e.g., Bayesian Information Criterion), where smaller numbers indicate a better fit, convergence (entropy > 0.80), the proportion of the sample in each latent class (not < 5%), posterior probabilities (mean probability of belonging in “most likely” class near 1.0), and the Lo-Mendell-Rubin adjusted likelihood ratio test (which is used to compare alternative models, e.g., k vs. k-1 classes) [53]. After a good fitting GMM model is found, the resulting latent classes will be described with respect to differences between initial CIPN symptom and functioning profile and change across time. Standard statistics (e.g., t-tests) will then be used to compare fall rates between the observed symptom and function latent classes. We will focus interpretation on effect sizes and 95% CIs. Beyond examining fall rates across the study time course, we will also explore survival models to predict time to first fall. Kaplan Meier models, Mantel-Cox log-rank tests and generalized Wilcoxon-Breslow tests will be used to evaluate differences in the distribution of time to first fall. Multivariate hazard ratios with 95% CIs and Wald χ2 statistics will be calculated from Cox models with Schoenfeld residuals used to test proportional hazards assumptions.

*Hypothesis 2.1. Sociodemographic (e.g., age, sex, comorbidities, body mass index), clinical (e.g., type of chemotherapy, # of chemotherapy cycles and/or cumulative dose of chemotherapy, disease stage, other symptoms), and mobility measures (gait and balance) can be used to predict distinct trajectories of change in neuropathy symptoms and functioning.*

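### The class-selection rule defines convergence as entropy above 0.80, but entropy measures how certain class membership is, not whether the estimation reached its best solution

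*Protocol article*

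**What the plan says.** In the protocol article, Specific analysis plan, the text under Hypothesis 1.2 describes the second modelling stage: "Each patient's intercept and growth estimates for each measure will be entered into a GMM". It then sets out how the number of classes is chosen: "Identification of the best-fitting model will be based on information criteria (e.g., Bayesian Information Criterion"), followed by four further items. These are convergence, a 5% floor on class size, posterior probabilities, and "the Lo-Mendell-Rubin adjusted likelihood ratio test (which is used to compare alternative models, e.g., k vs. k-1 classes").

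The only content given to convergence is the entropy cut-off: "where smaller numbers indicate a better fit, convergence (entropy > 0.80"). A separate item asks for a "mean probability of belonging in “most likely” class near 1.0". The article does not rank the five items, make any of them a veto, or say what happens when they disagree.

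Once a model is chosen, "the highest membership probability will be used to make a final class assignment". The assigned classes are then compared on fall rates and, under Hypothesis 2.1, related to the candidate predictors.

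**The concern.** A convergence criterion should tell the analyst whether the reported solution is the maximum of the likelihood or a local one. Entropy cannot do this. A fully converged model of moderately separated classes has low entropy, and a local solution with sharply divided groups has high entropy.

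The criterion therefore leaves the property it names unchecked, and it measures much the same thing as the posterior-probability item. It is also one of only two items with a numeric cut-off (the other is the 5% floor), so an analyst could readily treat 0.80 as a pass mark.

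The number and make-up of the classes decide Hypothesis 1.2 and supply the outcome for Hypothesis 2.1. If a local solution is accepted because its entropy is high, another analyst may not reproduce the classes. If a sound two-class model is set aside because its entropy is 0.70, the study may miss the structure it was designed to find.

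**Working it through.** **Inputs from the article.** Sample size/power calculation gives 2 symptom and 6 function measures in the most complex model, a 20:1 ratio, 160 complete cases, 200 participants and about 20% attrition. These figures agree with each other: 2 + 6 = 8; 20 × 8 = 160; 160 / 0.80 = 200. With an intercept and a linear slope per measure, the class model has 8 × 2 = 16 indicators. The 0.80 cut-off is a chosen threshold, so there is no derivation to reproduce.

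**Assumptions.** The article gives no class separation, class shares or indicator correlations, and says the model parameters are unknown. The values below are therefore a range, not a forecast.

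**Step 1: what entropy contains.** Relative entropy for n patients and K classes is E = 1 − [Σᵢ Σₖ (−pᵢₖ ln pᵢₖ)] / (n ln K), where pᵢₖ is the posterior probability of class k for patient i. Neither the log-likelihood nor the starting values enter it.

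**Step 2: separation needed for E > 0.80.** For two normal classes at Mahalanobis distance D, numerical integration gives these values at E = 0.80:

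| Class shares | D | SD per indicator, 16 indicators | SD per indicator, 8 indicators |
|---|---|---|---|
| 50/50 | 3.20 | 0.80 | 1.13 |
| 30/70 | 3.09 | 0.77 | 1.09 |
| 20/80 | 2.90 | 0.73 | 1.03 |
| 10/90 | 2.43 | 0.61 | 0.86 |

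For independent indicators the per-indicator difference is D / √(number of indicators), for example 3.20 / √16 = 0.80.

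**Step 3: good convergence with low entropy.** The simulation used n = 200, two true 50/50 classes, 16 independent indicators, 100 runs per row, and a latent profile model with equal diagonal variances and 20 random starts.

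| SD per indicator (D) | Starts reaching best log-likelihood | Mean entropy | Mean posterior probability | Two classes kept, BIC alone | Kept if BIC, E > 0.80 and the 5% floor are all required |
|---|---|---|---|---|---|
| 0.5 (2.0) | 98% | 0.57 | 0.87 | 22% | 0% |
| 0.6 (2.4) | 100% | 0.65 | 0.90 | 94% | 0% |
| 0.7 (2.8) | 100% | 0.74 | 0.93 | 100% | 5% |
| 0.8 (3.2) | 100% | 0.82 | 0.95 | 100% | 70% |
| 1.0 (4.0) | 100% | 0.92 | 0.98 | 100% | 100% |

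Convergence is essentially complete in every row, while entropy moves with D alone. Entropy and mean posterior probability rise together. The Monte Carlo standard error of the 70% figure is √(0.70 × 0.30 / 100) = 0.046.

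**Step 4: poor convergence with high entropy.** Two-class models were fitted to a single class of independent normals. With 8 indicators, 50% of starts reached the best log-likelihood and entropy exceeded 0.80 in 32% of runs. With 16 indicators the figures were 41% and 48%. A further check looked at three- and four-class fits to data simulated with d = 1.0, and at four-class fits to one correlated population. There, 83–97% of the local solutions that did not reach the best log-likelihood had entropy above 0.80.

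**Step 5: what low entropy does to the later comparison.** With equal classes, modal assignment misclassifies Φ(−D/2) of patients, and the difference between assigned classes is (1 − 2 × that share) of the true difference.

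- D = 2.4: Φ(−1.2) = 0.115, so the difference shrinks by 2 × 0.115 = 23%.
- D = 3.2: Φ(−1.6) = 0.055, so it shrinks by 2 × 0.055 = 11%.

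**The case against.** The strongest reply is that this is a loose label, not a faulty rule. The five items are to be weighed together and none is a veto, so the rejection percentages in Step 3 presuppose a use that the article does not prescribe. They also arise only at moderate separation: at 1.0 SD on 16 indicators every run passed. This stands, and those percentages should be read as conditional.

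A second reply is that a preference for high entropy is defensible here, because the plan assigns patients to their most likely class and then runs ordinary tests. Step 5 supports this. Lowering the entropy requirement while keeping modal assignment alone would dilute the fall-rate comparison, so the remedy has to address it.

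Third, an article condenses a longer document. The number of random starts and a log-likelihood replication check may well be in an analysis plan not shown here, so their absence is no finding. That does not rescue the criterion that is printed, because convergence is given a definition and the definition is wrong.

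A reader might also infer that the rule lets false classes through. In one correlated population (correlation 0.3, 16 indicators), BIC, entropy and the 5% floor were indeed all met in 98% of runs. But BIC supports the same false models, so the entropy wording is not the cause, and removing a criterion could not screen them out. With independent normal indicators the same three items together passed none. The Lo-Mendell-Rubin test, which is part of the stated rule, was not simulated, so the false-pass rate of the full rule is unknown. That inference is not made here.

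**Conclusion.** The point holds in a limited form. The convergence criterion is wrong as written: entropy above 0.80 neither shows that a model has converged nor, when absent, shows that it has not. This follows from the formula and needs no assumption about the data.

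The size of the consequence does depend on assumptions. If 0.80 were used as a requirement, with two equal classes, 16 independent indicators and n = 200, a correct two-class model would be kept in 0%, 5% and 70% of runs at 0.6, 0.7 and 0.8 SD per indicator, against 94%, 100% and 100% on BIC alone. At 1.0 SD there would be no loss. A reader might infer that the plan will discard correct models. The article does not support that, since it states no veto and gives no expected separation. It supports only that such rejection is possible under one natural reading of the cut-off.

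The overlap between entropy and mean posterior probability is redundancy and does no harm in itself. The change is still worth making before the class models are fitted, because Hypotheses 1.2 and 2.1 both rest on the chosen classes.

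**What to change.** 1. Define convergence as replication of the best log-likelihood over many random starts, with no inadmissible estimates, for each number of classes considered.
2. Relabel entropy, together with mean posterior probability, as a measure of classification quality. State that it does not by itself veto a model supported by BIC and the Lo-Mendell-Rubin test, and say how disagreements among the remaining criteria are settled.
3. If a model with entropy at or below 0.80 is kept, carry classification uncertainty into the fall-rate and predictor comparisons, for example with a three-step correction in Mplus (already the planned software), instead of relying on modal assignment alone.

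The cost is a few sentences of text, more computing time for the random starts, and a somewhat more complex later analysis when item 3 applies. No data collection changes. Item 3 should not be left out: without it, keeping a lower-entropy model would bring the dilution shown in Step 5.
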